### 2.5. Intervention

The study drug is dronabinol (Marinol®, AbbVie, Inc; Chicago, IL, USA). Eligible patients will receive adjunctive dronabinol vs. control (no dronabinol, systemic analgesia only). Patients will be allocated to a treatment in accordance with the randomization schedule following confirmation of eligibility. 

Patients who consent to participate in the study will have an order in the electronic medical record that will be used to assist with treatment compliance and for dispensing dronabinol, when applicable. Patients randomized to the dronabinol arm should receive their first dose within 12 h of randomization. The initial dosing and any changes in dosing will be determined by the prescribing/treating clinician. The target dose is 5 mg twice daily; the dose may be adjusted to within 5 mg to 30 mg daily in divided doses (e.g., 2.5 mg twice daily–10 mg three times daily). Patients who are randomized to the control arm will have an order set that specifies no administration of dronabinol for 48 h.

Patients in both arms will receive as needed (pro re nata, PRN) non-opioid/opioid analgesia as determined by the care team; patients who are not randomized to the dronabinol arm will receive these analgesics only, while patients randomized to the dronabinol arm will receive dronabinol in addition to PRN non-opioid/opioid analgesia. A target pain numeric rating score for trauma patients is 4 or less on a 0–10 scale. Higher pain scores ≥5 typically warrant analgesia, as determined by the attending physician and care team for the patient’s specific needs. These established guidelines will ensure patients are receiving analgesia based on self-reported pain, independent of treatment arm.

After the 48-hour treatment window post-randomization, the use of adjunctive dronabinol for the remaining acute hospitalization will be at the patient’s and physician’s discretion. Except for the analgesia protocol, all other interventions will follow techniques used in the context of everyday clinical practice, and thus will be identical for participants in both arms. The following medications are discouraged: neuraxial and locoregional nerve blocks.

### 2.6. Outcome Measures

Patients will be followed to hospital discharge for outcomes of morphine equivalent use, length of stay, pain NRS scores, hospital complications, and analgesic complications. 

The primary outcome is morphine equivalents. All opioids consumed will be converted to morphine equivalents, as shown in Figure 1 [11]. The clinical effects of treatment arm on morphine equivalents will be evaluated at 48 h after randomization. 

Secondary outcomes include the following:Morphine equivalents: overall (hospital admission through discharge or death)Non-opioid analgesics: overall doses received (admission through acute hospitalization discharge or death), and examined by non-opioid drugAcute hospitalization length of stayPain NRS scores: in ED prior to randomization, once admitted in hospital bed, preoperatively in the OR prior to anesthesia, one-hour post operatively, at hospital dischargeTime (hours) to transition to non-opioid analgesiaIncidence of hospital complicationsSafety (Incidence of analgesic complications)

Analgesic complications will be recorded irrespective of the presence or absence of a causal relationship, and include the including:Allergic reactionNausea and vomitingRespiratory depression (hypoxia and hypopnea)HypotensionUrinary retentionConstipation/ileusAbdominal painDizzinessEuphoriaParanoid reactionSomnolenceDeliriumOver-sedation.

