Recently published preliminary clinical research from our group examined the effect of adjunctive dronabinol for acute pain management among 66 trauma patients [10]. Cases demonstrated a significant reduction in opioid consumption (morphine equivalents) from baseline with adjunctive dronabinol (−79 mg, *p* < 0.001), while the change in opioid consumption for matched controls was unchanged from baseline (−9 mg, *p* = 0.63), resulting in a nine-fold greater reduction in opioid consumption for cases versus controls that was significantly different between pairs (difference: −70 mg, *p* = 0.02). There were no differences in secondary outcomes. These results suggest that adjunctive dronabinol used as part of a multimodal analgesia regimen may result in a marked reduction in opioid consumption

Two subset analyses of this matched cohort study provide mixed evidence that the opioid sparing effect of dronabinol may be greater in patients who are marijuana users. Among the subset of 19 cases who were marijuana users, opioid consumption was significantly reduced with adjunctive dronabinol (−97 mg, *p* < 0.001) versus no change in opioid consumption in 19 matched controls (1 mg, *p* = 0.70), with a difference between pairs that was significant: −108 mg, *p* = 0.01) [10]. However, when examining the subset of patients who received dronabinol, there were no differences in the change in opioid consumption for patients who were marijuana users (*n* = 21, −97 mg reduction with dronabinol) compared to non-marijuana users (*n* = 15, −64 mg reduction with dronabinol), *p* = 0.41 (unpublished). 

We are recruiting patients in a RCT to evaluate the efficacy of adjunctive dronabinol on opioid utilization for acute pain management. The primary trial objective is to evaluate the efficacy of adjunctive dronabinol versus control (systemic analgesics only, no dronabinol) for reduction in opioid consumption in adults with traumatic injury. Dronabinol is a licensed form of Δ^9^-THC. Dronabinol is not FDA approved for acute pain management; however, it has been in use at our level I trauma center system formulary without restriction since 2015. 

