### 2.7. Statistics

Significance is set at an alpha value of 0.05. SAS (Cary, NC) software will be used for statistical analysis. All efficacy analyses will be performed in the intent-to-treat population, defined as all patients who are randomized. Subset analyses will be performed by habitual marijuana use. 

The primary endpoint is the change in morphine equivalents and will be assessed as: post-randomization (48 h after randomization) minus pre-randomization (24 h prior to randomization). No imputation will occur for the primary endpoint. The change in morphine equivalents (mg) will be analyzed with an analysis of covariance (ANCOVA) model to examine the effect of treatment arm, adjusted for age, gender, injury severity score, and clinical characteristics that differ between groups with *p* < 0.15. Of note, our study inclusion criteria allow for patients to present with polytrauma. We anticipate the majority of patients will have injuries to the thorax and extremities, with few patients presenting with severe TBI because administration of opioids and other drugs that alter a neurological assessment tend to be used sparingly. Should there be differences in injury patterns, despite the 1:1 randomization procedure, these differences will be adjusted for in the primary ANCOVA analysis.

Secondary efficacy analyses include the difference between treatment groups in: hospital disposition, hospital complications, and analgesic complications, reported as proportion (%) and analyzed with chi-square tests; morphine equivalents over the hospitalization, hospital length of stay (days), time (h) to transition to non-opioid analgesia, pain NRS scores at all specified time points, reported as median (IQR) and analyzed with a Wilcoxon rank-sum test. Analgesic complications will be described by severity as mild, moderate and severe.

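### Analgesic complications are compared by arm up to discharge, but the arms differ by protocol for only 48 h; a comparison limited to those 48 h should be added

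*Protocol article*

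**What the plan says.** - **Follow-up.** Protocol article, section 2.6: "Patients will be followed to hospital discharge for outcomes of morphine equivalent use, length of stay, pain NRS scores, hospital complications, and analgesic complications". Section 2.3 agrees: analgesic complications are among the items recorded after randomization during the acute hospitalization.
- **Test.** Section 2.7 lists, among the secondary efficacy analyses by treatment group, "hospital disposition, hospital complications, and analgesic complications, reported as proportion (%) and analyzed with chi-square tests". The population is all randomized patients: "All efficacy analyses will be performed in the intent-to-treat population, defined as all patients who are randomized".
- **Exposure in the first 48 h.** Section 2.5 says that patients in the "control arm will have an order set that specifies no administration of dronabinol for 48 h".
- **Exposure afterwards.** The same section says that after the treatment window "the use of adjunctive dronabinol for the remaining acute hospitalization will be at the patient’s and physician’s discretion". No arm is named. Section 1 adds that "it has been in use at our level I trauma center system formulary without restriction since 2015", so the drug is available outside the trial order.
- **Primary endpoint, for contrast.** Sections 2.6 and 2.7 tie the change in morphine equivalents to 48 h after randomization.
- **Purpose.** The Discussion presents the recording and analysis of complications by arm and severity as an advance on the earlier matched cohort study.

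**The concern.** The efficacy window matches the period in which the protocol separates the arms. The stated follow-up for complications does not. It runs through a later period of variable length in which controls may start dronabinol and patients in the dronabinol arm may stop.

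A proportion of patients with any event by discharge pools both periods. It also takes no account of time at risk, although length of stay is itself a secondary outcome and may differ by arm. Several listed events, such as nausea, constipation and somnolence, can also be expected with opioids alone, so background events accumulate in both arms.

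At stake is how the safety result is read. A report of no difference in complications by discharge could be taken to mean that dronabinol added no harm while it was the randomized difference between the arms. The planned comparison need not support that.

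**Working it through.** **The plan's own figure.** The plan gives no complication rate, uptake after 48 h or power for this comparison, so there is nothing to reproduce. The only figure taken from it is the sample size in section 2.8: 122 randomized 1:1, or 61 per arm.

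**Assumptions (not from the documents).** The risk of an analgesic complication per 48 h is 20% on dronabinol and 5% off it. The stay lasts k = 1, 2 or 3 further 48 h periods (48, 96 or 144 h). A share u of an arm uses dronabinol in those later periods.

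**Formulas.**
- Risk in each later period: p_later = 0.05 + 0.15 × u.
- Risk of any event by discharge: 1 − (1 − p48) × (1 − p_later)^k.
- Power, two-sided 5%, n = 61 per arm: Φ[(d − 1.96 × se0) / se1]. Here d is the risk difference, p̄ the mean of the two risks, se0 = √(2 p̄(1 − p̄)/n) and se1 = √((p1(1 − p1) + p2(1 − p2))/n).

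**48 h window.** The risks are 5% vs 20%, so d = 0.15 and the risk ratio is 4.0. With p̄ = 0.125, se0 = 0.0599 and se1 = 0.0583. Power = Φ[(0.15 − 0.1174)/0.0583] = Φ(0.56) = 71%.

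**To discharge, half of each arm on dronabinol, k = 1.** p_later = 0.05 + 0.15 × 0.5 = 0.125.
- Control: 1 − 0.95 × 0.875 = 16.9%.
- Dronabinol: 1 − 0.80 × 0.875 = 30.0%.
- d = 0.131 and the ratio is 1.78. With se0 = 0.0767 and se1 = 0.0758, power = Φ(−0.25) = 40%.

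**All scenarios (k = 1 to k = 3).**

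| Use after 48 h, dronabinol arm vs control | Risk difference, points | Risk ratio | Power |
|---|---|---|---|
| 48 h window only | 15 | 4.0 | 71% |
| 50% vs 50% | 13 to 10 | 1.78 to 1.28 | 40% to 20% |
| None vs none | 14 to 13 | 2.46 to 1.69 | 56% to 37% |
| 70% vs 30% | 18 to 22 | 2.31 to 1.75 | 68% to 71% |
| 50% vs none | 20 to 28 | 3.08 to 2.50 | 81% to 92% |
| 100% vs none | 26 to 40 | 3.69 to 3.18 | 94% to 99.8% |

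**Reading the table.** Equal later use lowers both the risk difference and power. So does no later use in either arm, through background events alone. Where later use stays clearly higher in the dronabinol arm, the risk difference grows and power holds or rises. The risk ratio falls in every row, including the last, because events accumulate in both arms. A falling ratio alone is therefore not evidence of hidden harm.

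**Second set of assumptions.** With a 10% background risk per period and 20 points added on dronabinol, the 48 h comparison is 30% vs 10%, with power 80%. With one later period, 50% use in each arm gives 44% vs 28% and power 45%. Full continuation with no control use gives 51% vs 19% and power 97%. The pattern is the same.

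**The case against.** **The window is inferred.** Section 2.7 gives no window for complications. Section 2.6 attaches an explicit admission-to-discharge span to some secondary outcomes but not to these, and event windows often belong in an analysis plan, which is not shown here. An unseen plan could indeed add a 48 h analysis. Even so, section 2.6 positively states follow-up to discharge for analgesic complications, and section 2.7 states an arm comparison of proportions. To discharge is what the article fixes.

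**The to-discharge comparison is legitimate.** It keeps all randomized patients, answers a treatment-policy question and fits the real-world aim given in the Discussion. This stands, and it is why that comparison should be kept. Alone, however, it does not describe safety under the randomized exposure.

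**Dilution is not certain.** A reader might infer that the comparison is bound to be pulled toward no difference. The documents do not support that. They do not state that controls will receive dronabinol; that they may follows from the 48 h limit on the control order and a discretion clause that names no arm. With little control uptake and good continuation, follow-up to discharge gains power.

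**It is not the only safety information.** A reader might also take this to be the trial's sole safety comparison. Hospital complications are compared by arm as well, analgesic complications are described by severity (section 2.7), and safety outcomes go to the medical executive committee on an ongoing basis (section 2.9).

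**Conclusion.** The point holds in a limited form. The planned comparison of analgesic complications mixes the 48 h in which the protocol separates the arms with a later period of variable length and discretionary exposure. A finding of no difference by discharge would not by itself show safety during the treatment window.

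The direction and size of the effect cannot be fixed from the documents. Under the assumed 20% vs 5% risks, power ranges from 20% to above 99% according to later use and length of stay, against 71% for the 48 h window. The documents therefore support saying that a difference can be diluted. They do not support saying that it will be, or that harm will be missed. The primary endpoint is unaffected. This is a worthwhile and inexpensive improvement to the safety analysis.

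**What to change.** In sections 2.6 and 2.7:

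1. Add a comparison by arm, in all randomized patients, of the proportion with an analgesic complication with onset from randomization to 48 h. This matches the primary endpoint's window.
2. Keep the to-discharge comparison by arm alongside it, described as the treatment-policy result.
3. Report dronabinol use after 48 h in each arm, so that the to-discharge result can be interpreted.
4. Treat any grouping of later events by drug received as descriptive only. It is not randomized, and those who choose or are offered the drug may differ in risk.

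**Cost.** The onset time of each complication must be recorded. Section 2.3 already calls for the date, time and dose of dronabinol doses; recording of use after 48 h should explicitly cover both arms. The 48 h comparison will contain fewer events. It may also hold as little as 48 − 12 = 36 h of exposure, because section 2.5 allows the first dose up to 12 h after randomization. Events after 48 h in patients who continue dronabinol will appear only in the to-discharge comparison, which is a further reason to keep both.

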## 2. Materials and Methods

### 2.1. Study Design and Setting 

This is an open label RCT being performed at a single level I trauma center: St. Anthony Hospital in Lakewood, CO. This RCT was designed primarily to determine whether adjunctive dronabinol reduces opioid consumption compared to control. The study was designed with a stratified randomization by baseline marijuana use, which is intended to determine whether the treatment effect of dronabinol is greater in chronic marijuana users compared to recreational or non-marijuana users. This stratified randomization design was incorporated based on the gestalt that cannabis-based medication has a greater benefit for marijuana users.

There is a 48-hour screening/randomization window, a 48-hour treatment window, and a total participation period extending through the acute hospitalization. A description of the clinical trial is posted at ClinicalTrials.gov.

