### 2.2. Study Subjects

Patients are being recruited from the participating trauma center to which they are acutely presenting. A total of 122 adult trauma patients will be randomized 1:1 across 2 study arms: adjunctive dronabinol or control (systemic analgesics only), as shown in Figure 1. 

Patients should fulfill all of the following inclusion criteria:Male or female, 18 years to 65 years old (inclusive).Diagnosis of traumatic injury based on ICD10 diagnosis of S00-T14, which covers injuries to any region of the body.Moderately high initial morphine equivalent use ≥50 mg within a 24-hour window during the screening period. Opioids will be converted to morphine equivalents (mg) using an Equianalgesic conversion chart, Table 1 [11].Willing to disclose current marijuana status (current user (habitual/chronic or recreational), former user, never user).

Patients fulfilling one or more of the following criteria may not be enrolled in the study:Patients on a pain management agreementPatients who are nil per os (NPO) at the time of randomization or are expected to be NPO within the next 48 h, with the exception for a brief NPO period for surgical proceduresPatients who have received or are expected to receive neuraxial/locoregional blocks for pain within the next 48 hoursPatients with a known allergy or previous hypersensitivity reaction to dronabinol or sesame oilPatients prescribed dronabinol between arrival and prior to randomizationPregnancy or breast feedingIncarceration (presumed; patients are not arraigned until after hospital discharge).

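### Secondary drug totals start at admission rather than randomization, and time to transition off opioids is given a rank-sum test although some patients will have no observed time

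*Protocol article*

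**What the plan says.** All references are to the protocol article.

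- **Counting window.** Section 2.6 lists as a secondary outcome "Morphine equivalents: overall (hospital admission through discharge or death", and for non-opioid analgesics "overall doses received (admission through acute hospitalization discharge or death".
- **Timing of randomization.** Section 2.1: "There is a 48-hour screening/randomization window, a 48-hour treatment window, and a total participation period extending through the acute hospitalization". Section 2.3 places screening within 48 h of admission.
- **Entry threshold.** Section 2.2: "Moderately high initial morphine equivalent use ≥50 mg within a 24-hour window during the screening period".
- **Start of study drug.** Section 2.5: "Patients randomized to the dronabinol arm should receive their first dose within 12 h of randomization".
- **Analysis.** Section 2.7 names "morphine equivalents over the hospitalization, hospital length of stay (days), time (h) to transition to non-opioid analgesia", with the pain scores, as outcomes to be summarised by median and interquartile range and compared by Wilcoxon rank-sum. It names no covariates for these comparisons and no test for the non-opioid doses. It places every efficacy analysis in the intention-to-treat population of all randomized patients. Its only statement on imputation concerns the primary endpoint.
- **End of follow-up.** Section 2.6 follows patients to hospital discharge.

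**The concern.** There are two separate issues, both in the secondary outcomes.

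1. **The totals include time before treatment.** Drug given before randomization cannot respond to the assigned arm. The primary endpoint separates use before and after randomization; the secondary totals merge them. The pre-randomization part brings its own between-patient variation, and nothing in the stated rank-sum comparison removes it. A real reduction after randomization becomes harder to see.

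2. **Time to transition is not observed for everyone.** A patient who leaves hospital or dies while still taking opioids has no transition time. A rank-sum test over all randomized patients then needs an assigned value, and the article gives none. Dropping these patients departs from the plan's own intention-to-treat definition and selects on something that happens after randomization. Entering their discharge time counts leaving on opioids as a successful transition. Under either rule, arms with different lengths of stay can appear to differ in transition when they do not. A median of observed times alone would describe only those who transitioned.

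**Working it through.** **What follows from the document alone.** Screening precedes randomization, eligibility needs at least 50 mg in 24 h of screening, and dronabinol starts after randomization. Every admission-to-discharge opioid total therefore contains at least 50 mg untouched by treatment, over a pre-randomization period of up to 48 h. No such minimum is known for non-opioid doses.

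**The plan's own figure.** No power is stated for the secondary outcomes. The primary design (section 2.8: 38% vs 8% reduction, SD 58, two-sided 0.05, 80% power, N = 122) serves only as a reference scale.

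- n per arm = 2 × 58² × (1.960 + 0.842)² / 30² = 58.7, so 59 per arm and 118 in total. A t test needs 60 per arm, 120 in total.
- Power at 61 per arm: SE = 58 × √(2/61) = 10.50; 30/10.50 − 1.96 = 0.90; Φ(0.90) = 81.5% (t test 80.9%). The stated 80% is reproduced.

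**Dilution (illustration).** Let post-randomization use have SD 58 and a true difference of 30, and add pre-randomization use with SD s and correlation ρ. The difference stays at 30 and the SD becomes √(58² + s² + 2ρ·58·s). The assumed s is 0.5, 1 or 1.5 times 58.

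| s | SD of total, ρ = 0 | Power | SD of total, ρ = 0.7 | Power |
|---|---|---|---|---|
| none | 58.0 | 81.5% | – | – |
| 29 | 64.8 | 72% | 81.0 | 53% |
| 58 | 82.0 | 52% | 106.9 | 34% |
| 87 | 104.6 | 35% | 134.2 | 23% |

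These are normal-theory figures. They borrow the primary endpoint's difference and SD (whose unit the article does not state) for a different outcome, so only the direction carries over. The arms are balanced on s in expectation, so there is no shift in either direction.

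**Time to transition (simulation on assumed inputs).** 61 per arm, 1,500 runs. Transition time is exponential with mean 72 h in controls. Discharge time is gamma with shape 3 and mean 400, 150 or 90 h, independent of transition. This leaves 4%, 21% or 35% of controls never transitioning.

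Power with a transition rate ratio of 1.7 and equal stays:

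| Rule | 4% | 21% | 35% |
|---|---|---|---|
| Rank-sum, never-transitioners dropped | 62% | 39% | 22% |
| Rank-sum, discharge time as event | 69% | 64% | 55% |
| Rank-sum, tied worst rank | 69% | 67% | 59% |
| Log-rank, censored at discharge | 80% | 76% | 69% |

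Rejection rate with no true effect, stays 30% shorter in one arm (never transitioning 4% vs 8%, 21% vs 31%, 35% vs 46%):

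| Rule | 4% vs 8% | 21% vs 31% | 35% vs 46% |
|---|---|---|---|
| Dropped | 5% | 11% | 15% |
| Discharge time as event | 5% | 9% | 19% |
| Tied worst rank | 5% | 7% | 11% |
| Log-rank | 5% | 4% | 5% |

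With equal stays and no effect, all four rules reject in 4% to 6% of runs. The Monte Carlo standard error near 5% is √(0.05 × 0.95/1500) = 0.6 points. The distortion comes from unequal stays, and its direction depends on the rule. Dropping patients or using discharge time flatters the arm with shorter stays; a worst rank penalises it.

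**The case against.** - **Noise, not bias.** A reader might infer that counting from admission favours an arm. It does not. Section 2.4 hides allocation until eligibility and consent are settled, so earlier use is balanced in expectation. This stands, and limits the first issue to lost precision.
- **A rank test can be made to work.** A reader might infer that never-transitioners cannot be given any valid value. A tied worst rank is a coherent third option and keeps every randomized patient, as section 2.7 requires. This also stands.
- **Detail for the analysis plan.** Time origin and handling rules are often left to a document that is not shown here, so their absence is no fault. What remains is what the article itself fixes: the admission window, and a rank-sum test with median for a time that some patients will not have.
- **Death or early discharge looking opioid-sparing.** A reader might infer this from totals that stop at discharge or death. The article gives no death rate, and length of stay is a listed secondary outcome, so the dependence is open to view. Whole-stay opioid use is also a legitimate measure of utilization, and use per hospital day is a matter of preference.
- **Complications.** Nothing says that complications are counted from admission, and section 2.3 lists analgesic complications under post-randomization procedures.
- **Assumed sizes.** Apart from the 50 mg and the 48 h, every magnitude above is assumed. That is correct, and none of them should be read as a forecast.

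**Conclusion.** The point holds for three secondary outcomes: whole-stay morphine equivalents, whole-stay non-opioid doses (window only, since no test is named for them) and time to transition.

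The admission window places at least 50 mg of unaffectable use in each opioid total, compared without adjustment. This weakens the comparison without tilting it; the loss depends on variances that the article does not give. The transition outcome is the more serious part. If never-transitioners are dropped or given their discharge time, the result depends on length of stay. The simulated false-positive rates of up to 15% and 19% rest on the assumed 30% difference in stay and on more than a third of patients leaving on opioids; with equal stays there is no excess. The log-rank result was obtained with discharge independent of transition, which suits that test.

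The primary endpoint uses windows on either side of randomization, and the sample size rests on it. Neither is affected. The change is worth making because it is cheap and concerns stated choices, but it does not threaten the trial's main conclusion.

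**What to change.** 1. Count morphine equivalents and non-opioid doses from randomization to discharge or death. The admission-to-discharge total may stay as a descriptive figure.
2. Measure time to transition from randomization and analyse it as time-to-event by **one** prespecified method. The two candidates answer different questions:
   - a cause-specific log-rank test, censoring at discharge or death on opioids, compares the rate of transition among patients still in hospital and on opioids;
   - cumulative incidence with Gray's test, treating those exits as competing events, compares the proportion who transition in hospital, and so still reflects length of stay.
3. If the rank test is kept, give never-transitioners a tied worst rank and say that this too responds to differences in stay.

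No change is needed for analgesic complications.

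The cost is minor rewording and programming. The primary endpoint already requires opioid use to be split at randomization. Section 2.3 specifies date and time only for dronabinol doses, so check that other analgesic records carry enough timing, above all the non-opioids and the moment of transition. Settle the wording before the interim analysis in section 2.9 (n = 62), because section 2.4 leaves the statisticians unblinded and a later choice could appear to be guided by results.

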### 2.3. Study Visits

The following procedures will be performed at screening, within 48 h of hospital admission: ensure patient meets inclusion and exclusion criteria; record 24-hour total morphine equivalents; record habitual marijuana usage; obtain informed consent via patient or proxy. 

Once patients are confirmed to meet all criteria and have signed an informed consent, they will be randomized 1:1 across the two study arms (dronabinol or control, Figure 1). The following procedures will be performed during randomization: randomize the patient using the Microsoft Excel blinded randomization schema; record pain using the patient self-reported pain numeric rating scale (NRS, 0–10 scale). 

The following procedures will be performed during the acute hospitalization, post-randomization: if randomized to the dronabinol arm, administer the first dose within the first scheduled dose window and within 12 h of randomization. Record all doses received, including date, time and dose; record all opioid and non-opioid systemic analgesics received, including route/dose/frequency; record all non-analgesic concomitant medications; record pain NRS scores at the following time points: once admitted in hospital bed, preoperatively in the OR prior to anesthesia, one hour post operatively; record all analgesic complications; record all documented drug use from patient self-report and urine drug screening results. Detailed information on the regularity of marijuana use will also be recorded. 

The following procedures will be performed at hospital discharge: record discharge pain NRS score; record discharge location; re-consent, if necessary. 

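### The pre-treatment pain score is defined differently in sections 2.3 and 2.6, at least one pre-randomization score is tested as efficacy, and the score collected at randomization has no named use in the pain analyses

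*Protocol article*

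**What the plan says.** Three sections of the protocol article bear on the pain score.

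- **Section 2.3 (Study Visits)** lists among the procedures at randomization: "randomize the patient using the Microsoft Excel blinded randomization schema; record pain using the patient self-reported pain numeric rating scale". Its post-randomization procedures then name three scores: "once admitted in hospital bed, preoperatively in the OR prior to anesthesia, one hour post operatively". At discharge the instruction is "record discharge pain NRS score". No ED score appears.
- **Section 2.6 (Outcome Measures)** makes pain a secondary outcome at five points. The list begins "in ED prior to randomization, once admitted in hospital bed" and continues with the preoperative, one-hour postoperative and discharge scores. The score taken at randomization is not in the list.
- **Section 2.7 (Statistics)** introduces a list with "Secondary efficacy analyses include the difference between treatment groups in", and that list includes "pain NRS scores at all specified time points, reported as median (IQR) and analyzed with a Wilcoxon rank-sum test". No covariate is named for these comparisons. The primary model for morphine equivalents, by contrast, is "adjusted for age, gender, injury severity score, and clinical characteristics that differ between groups with" p < 0.15.

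**The concern.** The four later points agree between sections 2.3 and 2.6; only the pre-treatment score differs. The two candidates are the same measurement only for a patient randomized in the ED. Otherwise they can be many hours apart. Section 2.1 allows 48 h for screening and randomization, and section 2.2 requires at least 50 mg morphine equivalents within a 24-hour window before entry. An ED score may therefore describe pain before much of that opioid was given.

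Separately, sections 2.6 and 2.7 together turn a score labelled as pre-randomization into an efficacy comparison. This would be so even if section 2.3 agreed with section 2.6.

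At stake is the reading of pain, the outcome that shows whether any fall in opioid use came without worse pain. The trial is open label, so a baseline clearly fixed before allocation is worth having. Entry no longer requires a minimum pain score (Trial Status), so pain at the start may vary widely.

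**Working it through.** **The plan's own figures.** None concerns pain. The one computed figure is the sample size for morphine equivalents, and this point does not depend on it. Reading the standard deviation of 58 in section 2.8 as percentage points, the difference is 38 − 8 = 30 and the standard error with 61 per arm is 58 × √(2/61) = 10.50. Power is Φ(30/10.50 − 1.96) = Φ(0.90) ≈ 0.815, in line with the stated 80%.

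**Step 1: the time points side by side.**

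| Pain score | Section 2.3 | Section 2.6 | Tested under section 2.7, read literally |
|---|---|---|---|
| ED, before randomization | not listed | listed | yes |
| At randomization | listed | not listed | not as a listed outcome |
| Hospital bed | listed as post-randomization | listed | yes |
| Preoperative | listed as post-randomization | listed | yes |
| One hour postoperative | listed as post-randomization | listed | yes |
| Discharge | listed | listed | yes |

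**Step 2: what a test of a pre-randomization score can show.** Under valid randomization the arms differ there only by chance, so the rejection rate is the nominal 5%. A simulation of the Wilcoxon test gave 4.7% (5,000 runs, 61 per arm; assumed scores: normal with mean 7 and standard deviation 2, rounded to the 0–10 scale).

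**Step 3: how many of the five comparisons this touches.** The ED score is pre-randomization by its own label. Section 2.3 lists the hospital-bed score as post-randomization, but randomization may follow admission by up to 48 h, so a patient may already be in a bed, or have had surgery, before being randomized. If the hospital-bed score preceded randomization in everyone, two of the five tests would carry no treatment information. The chance of at least one false positive would then be 1 − 0.95² = 9.75%, taking the two as independent. The documents do not say how often this happens. Where it happens in only some patients, the comparison mixes pre- and post-randomization values.

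**Step 4: precision lost without adjustment.** With correlation r between baseline and later score, linear adjustment multiplies the variance of the arm difference by 1 − r². The document gives no r, so the range is an assumption.

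| Assumed r | Variance reduction, r² | Standard error factor, √(1 − r²) |
|---|---|---|
| 0.3 | 9% | 0.95 |
| 0.5 | 25% | 0.87 |
| 0.6 | 36% | 0.80 |

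These ratios need no assumed standard deviation or number of patients. That is useful because the preoperative and postoperative scores exist only for patients who have surgery, so 61 per arm cannot be assumed there.

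**Step 5: is the randomization score a clean baseline?** Section 2.3 names the randomization step first and the pain score after it, and section 2.4 states that participants, treatment team and assessors are unblinded. Nothing says the score is taken before the arm is known.

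**The case against.** The other side has real force on several points.

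- **Validity.** An unadjusted Wilcoxon test of a post-randomization score in a randomized trial is valid. Chance imbalance at baseline is already in its error rate. A reader might infer that the later pain comparisons are biased. They are not; they are only less precise than they could be. This stands.
- **Use of the randomization score.** A reader might infer that the plan never uses it. The text does not support that. The p < 0.15 rule could bring it into the primary model, and descriptive use may be set out in a fuller protocol or analysis plan that is not shown. What can be said is that the article names no use of it in the pain analyses. The p < 0.15 rule does not repair those, because it applies only to the morphine-equivalent model and only if an imbalance appears.
- **Which score is the true baseline.** A reader might want simply to put the randomization score in place of the ED score. Step 5 shows the risk: a self-reported score taken after allocation is known could already reflect the arm, and adjusting for it would be unsafe. The ED score is the only one labelled as preceding randomization.
- **Size of the gain.** Both arms receive analgesia as needed towards a target score of 4 or less (section 2.5), which may weaken the correlation between baseline and later pain. The upper end of the range in step 4 is therefore not assured. Power figures for pain would need a standard deviation and an effect size that the document does not give.
- **Impact.** Because the ED score carries its label, an alert reader would take a difference there as baseline imbalance. That limits the harm but does not make it sensible to list the comparison as efficacy.

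**Conclusion.** The point holds for a secondary outcome and is worth correcting. Two parts rest on the text alone: sections 2.3 and 2.6 name different pre-treatment pain scores, and section 2.7 read literally tests at least one pre-randomization score as efficacy, at a nominal 5% false-positive rate with no possible true effect. That the hospital-bed score, and possibly the perioperative scores, precede randomization in some patients follows from the 48 h window, but its frequency is unknown. The cost of leaving later scores unadjusted is precision only, about 9% to 36% of the variance for an assumed correlation of 0.3 to 0.6. The primary endpoint, the sample size and the interim rule are unaffected.

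**What to change.** 1. In sections 2.3 and 2.6, name one baseline pain score: the last score recorded before allocation is revealed. State in section 2.3 that the randomization-visit score is taken before the arm is known. For patients already enrolled in whom this was not so, use the last earlier score.
2. In section 2.6, classify each pain score as pre- or post-randomization by its actual recorded time, not by its place in a list of visits.
3. In section 2.7, report the ED score and every other score taken before randomization descriptively, with no efficacy test.
4. Compare post-randomization scores with adjustment for the baseline score, by ANCOVA or rank ANCOVA, and keep the Wilcoxon test as a sensitivity analysis.

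The cost is wording in three sections and one covariate. A randomization score is already collected and section 2.4 describes pain scores as routine nursing records, so no new assessment is needed, assuming those records carry times. The small downside is that the main pain result becomes an adjusted difference in place of a simple comparison of medians.
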